### Objectives

The primary objective of TB SCRIPT is to compare the impact of POC CRP-based with symptom-based TB screening on 2-year TB disease outcomes. We will randomize participants to either POC CRP-based (intervention) or standard-of-practice symptom-based TB screening (control). All participants who screen positive will undergo confirmatory TB testing, while only participants who screen negative will initiate 12 weekly doses of isoniazid and rifapentine (3HP), a short-course TPT regimen. We will follow all eligible participants for 2 years to assess TB incidence and all-cause mortality. At the final study visit, we will collect sputum to ascertain active TB status from participants who have not been diagnosed with or treated for active TB during follow-up. The primary hypothesis for this objective is that participants randomized to POC CRP-based TB screening will have lower combined 2-year TB incidence and mortality (composite primary trial outcome), relative to participants randomized to symptom-based screening. The second objective is to compare the impact of POC CRP-based with symptom-based TB screening on (1) TPT uptake and (2) prevalent TB case detection, intermediate outcomes on the pathway to the combined primary trial outcome. The primary hypothesis for this objective is that participants randomized to POC CRP-based TB screening will have higher rates of TPT uptake and completion, determined via objective monitoring, and similar rates of prevalent TB case detection relative to participants randomized to symptom-based screening.

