#### Intervention arm: POC CRP-based TB screening

For participants randomized to POC CRP-based TB screening, we will record POC CRP concentrations measured from capillary blood obtained via finger prick using a standard sensitivity POC assay (iCHROMA CRP assay; BodiTech, South Korea). The iCHROMA CRP assay is a US Food and Drug Administration (FDA)-approved, fully quantitative, lateral flow-based fluorescence sandwich immunoassay with a detection range of 2.5–300 mg/L and excellent stability after more than 18 months of storage under the recommended conditions.

Although the recent WHO TB screening guidelines recommend using a cut-point of 5 mg/L to maximize sensitivity of CRP for active TB, we selected a cut-point of 8 mg/L prior to the updated WHO recommendations based on our own previously published research demonstrating a CRP cut-point of 8 mg/L to have 90% sensitivity and 70% specificity for culture-confirmed TB [20, 26, 27]. Participants with POC CRP levels ≥8 mg/L will be classified as screen-positive while those with POC CRP levels < 8 mg/L will be classified as screen-negative.

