**D. Prevalent TB diagnosis**		
Number microbiologically confirmed prevalent TB cases detected by the screening test	# screen-positives diagnosed with prevalent TB (diagnosed = a positive urine LAM result, one non-trace positive or two trace-positive Xpert Ultra results ≤3 months of study entry)	
Proportion microbiologically confirmed prevalent TB cases detected by the screening test	# screen-positives diagnosed with prevalent TB	# randomized to corresponding study arm
Number microbiologically confirmed prevalent TB cases missed by the screening test	# screen-negatives diagnosed with prevalent TB	None
Proportion microbiologically confirmed prevalent TB cases missed by the screening test	# screen-negatives diagnosed with prevalent TB	# randomized to corresponding study arm
Number diagnosed with microbiologically confirmed prevalent TB	# screen-positives diagnosed with prevalent TB + # screen-negatives diagnosed with prevalent TB	None
Microbiologically confirmed TB prevalence	# screen-positives diagnosed with prevalent TB + # screen-negatives diagnosed with prevalent TB	# randomized to corresponding study arm

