To evaluate intermediate outcomes on the pathway to the composite primary trial outcome, we will determine the proportion of randomized participants initiating TPT (prescribed TPT), the proportion of randomized participants completing TPT (≥90% TPT pills taken), the proportion of randomized participants diagnosed with prevalent TB, and the proportion of randomized participants with prevalent TB completing TB treatment (by clinic record review). The primary analysis will be by ITT, with the outcome of initiating any TPT based on actual events, irrespective of whether the algorithm was followed. Participants eligible for 3HP based on the results of baseline screening (i.e., study-initiated TPT) may decline to initiate 3HP after randomization despite being prescribed 3HP; these participants will be counted as not having started TPT. Participants who were initiated on TPT during study follow-up (i.e., clinician-initiated TPT for participants who were classified as ineligible for 3HP based on the results of baseline screening) will be counted as having started TPT; 6 months of daily isoniazid (IPT) is currently the most common TPT regimen available for routine clinical use. We will compare the proportion of PLHIV initiating any TPT (study- and clinician-initiated TPT) and the proportion of PLHIV completing TPT (the denominator will be the total number of participants in the study arm), calculating the risk difference and 95% confidence intervals (CI) using standard methods, adjusted for study site using Cochran-Mantel-Haenzsel weights. If respective data on an outcome is missing or a patient is lost to follow-up, it will be assumed that the patient did not initiate nor complete TPT (depending on what data are available). Our working hypothesis is that POC CRP-based TB screening will increase the proportion of PLHIV initiating and completing TPT by at least 40%, relative to symptom-based screening. We will compare the proportion of PLHIV with screen-positive prevalent TB and the proportion of PLHIV with screen-positive prevalent TB completing TB treatment, calculating the risk difference and 95% CIs using standard methods, adjusted for study site using Cochran-Mantel-Haenszel weights. Our working hypothesis is that the proportion of PLHIV with screen-positive prevalent TB will be similar in each arm, and we expect the upper bound of the CI of the difference will be no more than 5%. We consider this margin of 5% sufficiently small to conclude equivalence.

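### Equivalence in prevalent-TB detection is to be concluded from the upper confidence limit alone, with no direction given for the difference, so on the natural reading no shortfall of CRP screening can fail

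*Protocol article*

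**What the plan says.** The second objective expects "similar rates of prevalent TB case detection relative to participants randomized to symptom-based screening" (Objectives). The analysis is set out in Statistical methods, Primary and secondary outcomes: "We will compare the proportion of PLHIV with screen-positive prevalent TB", "calculating the risk difference and 95% CIs using standard methods, adjusted for study site using Cochran-Mantel-Haenszel weights". The criterion follows: "we expect the upper bound of the CI of the difference will be no more than 5" (per cent), and then "We consider this margin of 5% sufficiently small to conclude equivalence".

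Table 2, part D, defines the outcome "Proportion microbiologically confirmed prevalent TB cases detected by the screening test". Its numerator is screen-positive participants diagnosed with prevalent TB. Its denominator is the number "randomized to corresponding study arm", that is, the whole arm and not the participants who have TB.

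The article gives no lower limit, no direction of subtraction, no expected prevalence or detection rate, and no power for this comparison.

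**The concern.** An equivalence claim needs both confidence limits inside the margin. A rule that looks only at the upper limit controls error on one side, and which side depends on the order of subtraction. That order is not stated.

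The side matters here. The worry with a more specific screen is that it detects fewer TB cases, not more. Under Risks to study participants, the article itself notes that missed cases may be started on preventive therapy, with a risk of acquired drug resistance. Confirmatory testing at baseline goes only to screen-positives, so a case missed by the screen is counted only if it is diagnosed in some other way within 3 months. The between-arm comparison of detected cases is therefore important randomized evidence on lost cases, and its success rule should be able to fail when cases are lost.

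**Working it through.** **Plan's own figure.** The article states power for the primary composite only. With 860 × 0.88 = 757 evaluable per arm, 12.5% v 8.1% and two-sided 0.05, power comes out at 0.80, as stated. There is no figure to reproduce for prevalent-TB detection.

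**Inputs.** From the document: 860 per arm (Sample size), risk difference with 95% CI, margin 5 points, denominator all randomized. Assumed: the control-arm detection rate p_S, run from 5% to 20% because the document gives none. A simple Wald interval without site adjustment is used:

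SE = √{[p_S(1−p_S) + p_C(1−p_C)] / 860}, with limits difference ± 1.96 × SE, where p_C is CRP-arm detection.

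**Reading 1: CRP minus symptom, upper limit ≤ 5.** Suppose CRP detects one-third fewer cases, p_C = (2/3)p_S. At p_S = 10%, p_C = 6.67%, the difference is −3.33 points and SE = √[(0.0900 + 0.0622)/860] = 0.0133. The CI is −3.33 ± 2.61, or −5.9 to −0.7.

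| Control detection | 95% CI, CRP minus symptom (points) | Upper limit ≤ 5? | Lower limit ≥ −5? |
|---|---|---|---|
| 5% | −3.6 to +0.2 | yes | yes |
| 10% | −5.9 to −0.7 | yes | no |
| 15% | −8.1 to −1.9 | yes | no |
| 20% | −10.2 to −3.2 | yes | no |

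Every row passes the rule as written. At 10% and above the interval also excludes zero, so a significant deficit would be called equivalence. A 90% loss passes too: at 10% control detection its CI is −11.1 to −6.9. In simulation, a true one-third loss passes with probability of about 1.00 for control detection from 5% to 15%.

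**Reading 2: symptom minus CRP, upper limit ≤ 5.** This does guard against lost cases, but it is a non-inferiority test: any excess under CRP passes. Solving (p_S − p_C) + 1.96 × SE = 0.05 gives the largest observed loss that still passes. The same figures apply to a corrected rule that requires the lower limit of CRP minus symptom to be at least −5.

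| Control detection | Lowest passing CRP detection | Loss (points) | Loss relative to control | Chance of passing if the true loss is one third |
|---|---|---|---|---|
| 5% | 1.7% | 3.3 | 66% | 0.93 |
| 8% | 5.4% | 2.6 | 33% | 0.49 |
| 10% | 7.7% | 2.3 | 23% | 0.24 |
| 15% | 13.3% | 1.7 | 11% | 0.03 |
| 20% | 18.7% | 1.3 | 6% | 0.002 |

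Check at 10%: 2.32 + 1.96 × 1.368 = 5.00 points. With 757 instead of 860 per arm, the relative-loss limits move by about 1 to 3 percentage points.

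The second table also shows what an absolute margin on the whole arm means. Five points is all of a 5% control yield (5/5), half of a 10% yield (5/10) and a third of a 15% yield (5/15).

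**The case against.** The sentence sits beside a hypothesis of similarity, calls 5% a margin and speaks of equivalence. A fair reader may take it to mean that the arms differ by no more than 5 points either way, and may expect an unseen analysis plan to fix the direction. That is probably what was intended. But the article does not stay silent on the rule: it names one limit and draws a conclusion from it, and neither order of subtraction makes that limit sufficient for the conclusion.

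A reader might infer more: that CRP screening could be declared equivalent while missing a third or more of TB cases at any prevalence. The document does not support this in general. It is true at any prevalence only under CRP minus symptom. In the other direction, or with both limits tested, a one-third observed loss relative to symptom screening passes only when control detection is about 8% or lower. Turning that into sensitivities would need a TB prevalence, which is not given, and a sensitivity for the symptom screen, which is not given either. The figure of "90% sensitivity and 70% specificity for culture-confirmed TB" describes CRP at the 8 mg/L cut-point.

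It is also fair to say that this comparison is not the only safeguard. Missed prevalent TB is a separate outcome, is tabulated by arm and is reviewed by the Data Monitoring Committee, and deaths enter the primary endpoint. These protections are partial, because screen-negatives have no confirmatory test at baseline and the article states no numerical limit for the committee.

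**Conclusion.** The rule as written does not support a conclusion of equivalence. This follows from the wording and needs no assumption about prevalence: one order of subtraction leaves lost cases unlimited, and the other is non-inferiority. The size depends on the order and on the control detection rate. Under CRP minus symptom, any shortfall passes. Under a correctly directed rule, the largest passing observed loss relative to symptom screening is about a third at 8% control detection, 23% at 10% and 11% at 15%, with 860 per arm and an unadjusted Wald interval.

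The breadth of a 5-point margin at low yield is a separate limitation that testing the second limit does not remove. Prevalent-TB detection is an intermediate outcome, and the primary superiority analysis, its alpha and its sample size are untouched. The point should be fixed before the analysis, but it does not threaten the trial's main result.

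**What to change.** Define the difference as CRP minus symptom screening. Then choose one of two rules:

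- equivalence, with both 95% limits within −5 to +5 points; or
- non-inferiority, named as such, with the lower 95% limit above −5 points.

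In either case, also report the ratio of yields (CRP/symptom) with its CI, and state what share of the cases detected in the control arm the margin allows to be lost. This does not turn 5 points into a strict margin at low yield, but it lets readers see what was ruled out.

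The cost is wording and a harder equivalence claim. If true detection is 10% in both arms, the chance of passing one limit is 0.933. Requiring both gives 1 − 2 × (1 − 0.933) = 0.87. At 15% it falls from 0.827 to 1 − 2 × (1 − 0.827) = 0.65. The non-inferiority option keeps the one-limit figures. Tightening the margin itself is not realistic at this size: at 10% detection in both arms, 80% power and one-sided 0.025, a 2-point margin would need about 3,530 per arm, against about 566 for 5 points.

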### Participant timeline

After baseline study procedures, routine clinic staff will provide all further care and follow-up for HIV, TPT, and/or active TB treatment. Routine clinical care for all patients initiated on ART includes blood draw for pre-ART labs, HIV viral load at 6 months and as appropriate thereafter, and clinic visits at weeks 2 and 6 and then months 3, 6, 12, 18, and 24 post-ART initiation. Patients initiated on 3HP or TB treatment have additional visits for active TB screening, medication adverse event (AE) monitoring, adherence assessments, and refills, per routine clinic protocols. To capture clinical and outcome data for this trial, we will conduct brief follow-up interviews and extract relevant data from the clinic medical record at regular intervals for 2 years (months 3, 6, 12, 18, and 24). At the final (24-month) study visit, we will collect sputum specimens from all participants who have not been treated for TB during the study for the final active TB assessment. Table 1 describes the schedule of study activities performed by study staff and the schedule of clinic activities performed by routine clinic staff for PLHIV initiating ART.

**Table 1 Tab1:** Schedule of study activities

Timepoint	Entry	Weeks				Months						
	0	2	4	6	8	3	4	5	6	12	18	24

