***Participants initiated on anti-TB therapy***												
AE monitoring		•	•		•	•	•	•	•			
TB treatment adherence monitoring		•	•		•	•	•	•	•			
Medication refills		•	•		•	•	•	•	•			

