### Blinding

TB SCRIPT is a single-blinded trial. We will not be blinded to intervention allocation, as we will perform baseline TB screening and subsequent procedures based on the results of screening (e.g., 3HP initiation for eligible screen-negative participants). Participants and routine clinic staff will be blinded, as will the study principal investigators (except for the trial statistician). To facilitate blinding, all participants will undergo a finger prick and have capillary blood measured for CRP (intervention) or beta-human chorionic gonadotropin (β-hCG; control, regardless of gender). POC CRP and β-hCG assays will be provided by BodiTech, Med Inc. and measured using the iCHROMA Reader which provides analysis of more than 30 unique markers, including CRP and β-hCG. There are no procedures for unblinding, as clinicians are free to order TB testing, initiate TB treatment, or initiate TPT for study participants at any time.

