We will repeat the primary analysis in the following pre-specified sub-groups: by age, gender, enrollment site, and CD4 strata (< 50, 50–199, ≥200 cells/μL). Safety data related to missed diagnoses of prevalent TB, acquired drug-resistant TB, and TPT-related serious adverse events will be tabulated by study arm.

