### Oversight and monitoring

The study will be overseen by an Administrative Core, chaired by the principal investigator and Uganda site principal investigator. In addition, a Clinical Trial Core chaired by two principal investigators will be responsible for maintaining ethics approvals, databases, and study monitoring. An Economic Modeling Core chaired by a principal investigator will be responsible for overseeing all economic and costing analyses.

The study team meets bi-weekly via conference calls to monitor the progress of the study, participant enrollment, and retention. Bi-weekly conference calls include a review of trial outcomes, as well as factors external to the study (e.g., scientific developments, COVID-19) that could impact the safety of study participants and/or study activities. Additional monthly conference calls separately review all adverse events and protocol deviations.

Day-to-day data and safety monitoring is the responsibility of the principal investigators and will follow guidelines established by IRBs regarding reportable adverse events (AE). Reportable AEs are reported to the IRBs within 10 days of study awareness. Reportable AEs will be attributed to the study intervention by the principal investigator with review by the physicians/co-investigators according to the following categories: definite, probably, possible, unlikely, and unrelated. A bi-annual and annual report of all reportable AEs will be presented to the Data Monitoring Committee (DMC) and National Heart, Lung and Blood and Institute, respectively. In addition, an endpoint adjudication committee will meet annually to review all deaths and determine causes of death.

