### Data monitoring committee

An independent DMC that includes experts in TB diagnostics and the analytical and regulatory aspects of clinical trials met by conference call before enrollment and will meet at 25%, 50%, 75%, and 100% enrollment and when 50% of patients have completed follow-up and when 100% have completed follow up to review safety data from the trial. They are charged with evaluating the quality of trial administration, monitoring safety issues, and providing guidance on scientific, methodological, and ethical issues. Specifically, the DMC will review administrative reports prepared by the Data Manager for each meeting of the DMC. This report will describe study progress, including the following: (1) accrual, (2) demographics, (3) subject status, (4) TB prevalence, (5) proportion of patients initiating TPT, (6) number and type of serious AEs (SAE), (7) cumulative TB incidence (including drug-resistant TB), and (8) cumulative all-cause mortality. Tables by arm will be prepared for review in the closed sessions of the DMC meetings; the DMC will have access to screening assignments. Differences in the composite primary trial outcome (2-year TB incidence and 2-year mortality) between trial arms are unlikely to modify our study protocol because of the long duration of follow-up (2 years), relative to recruitment. However, differences in missed diagnoses of prevalent TB (primary risk and safety endpoint), measured as the proportion of microbiologically confirmed prevalent TB cases missed by screening, will be carefully reviewed and the decision to continue enrollment after each meeting will be made by the DMC. Although unlikely, the DMC should inform the PIs if, in their view, the results of an interim analysis are likely to convince a broad range of clinicians (including those supporting the trial and the general clinical community) that, on balance, one trial arm is clearly indicated or contraindicated for all participants or a particular category of participant. Further details of stopping guidelines and roles and responsibilities of members are included in the DMC charter.

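### The planned analysis tabulates by arm only the serious adverse events judged related to preventive therapy, and the stated causality rule does not produce that judgement

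*Protocol article*

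**What the plan says.** All references are to the protocol article.

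- **Statistical methods, last paragraph.** The planned safety analysis is one sentence with three items. Two are TB outcomes: missed prevalent TB and acquired drug-resistant TB. The third is the only adverse-event category: "TPT-related serious adverse events will be tabulated by study arm".
- **Oversight and monitoring.** The causality rule is "Reportable AEs will be attributed to the study intervention by the principal investigator", with review by physicians and co-investigators, on a five-level scale from definite to unrelated.
- **Interventions.** The intervention is point-of-care CRP screening and the control is the four-symptom screen. Both are screening strategies. Screen-negative, eligible participants in either arm are offered 3HP.
- **Blinding.** "Participants and routine clinic staff will be blinded, as will the study principal investigators", apart from the trial statistician.
- **Data monitoring committee.** The report to the DMC includes serious adverse events by number and type, without restriction to TPT, and "Tables by arm will be prepared for review in the closed sessions of the DMC meetings".
- **Participant timeline.** "Patients initiated on 3HP or TB treatment have additional visits for active TB screening, medication adverse event (AE) monitoring".
- **Table 1.** The only adverse-event monitoring row stands under the heading "Participants initiated on anti-TB therapy". The TPT rows for screen-negative participants list adherence monitoring only.

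**The concern.** The trial compares two screening strategies. Each can lead to TPT, to TB treatment or to neither, so a safety comparison by strategy should count serious events wherever on those pathways they occur. The stated analysis counts them on one pathway only, and only after someone has judged them TPT-related. The arm designed to give more TPT will then show more events. A reader of the final report could not see from that table whether total serious events differ between the strategies.

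The judgement that decides which events enter the table is not the one the article describes. Attribution is made to the intervention, but the table needs attribution to a class of drugs used in both arms. If the rule is left as it is, different assessors could fill the table in different ways.

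The mismatch between the text and Table 1 on 3HP monitoring is a smaller matter. It concerns how the events that feed this table are collected.

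**Working it through.** The article states no expected number or risk of serious adverse events, so there is no safety figure to reproduce. The check has one short calculation and two comparisons of text.

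**1. How the count divides between arms by design**

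Inputs, all from the section on sample size: 860 participants per arm; at most 15% of the control arm and an anticipated 55% of the CRP arm start 3HP.

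- Expected starters, CRP arm: 860 × 0.55 = 473.
- Expected starters, control arm: 860 × 0.15 = 129.
- Ratio: 473 / 129 = 3.67.

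Let r be the risk of a TPT-related serious event per starter, assumed equal in both arms. The documents give no value, so a range is shown. Expected events are 473 × r and 129 × r.

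| Assumed r | CRP arm | Control arm |
|---|---|---|
| 0.5% | 2.4 | 0.6 |
| 1% | 4.7 | 1.3 |
| 2% | 9.5 | 2.6 |
| 3% | 14.2 | 3.9 |
| 5% | 23.7 | 6.5 |

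At r = 2%, the table would show 9.5 / 860 = 1.1% against 2.6 / 860 = 0.3% of those randomized, although risk per starter is the same. The ratio stays at 3.67 whatever r is. It covers 3HP starters only. TPT started later by routine clinicians in screen-positive participants would add takers in either arm and could change it.

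**2. Whether the causality rule feeds the table**

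- Required by the statistical methods: each serious event classed as TPT-related or not, in both arms.
- Supplied by the oversight section: each reportable event graded for its relation to the study intervention.
- Meaning of that term in the section on interventions: CRP-based screening.

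Take a control participant who has a serious reaction to 3HP. Read literally, that person never received the intervention, so grading the event against it says nothing about TPT. For a CRP participant with the same reaction, the grade could mean relation to the screen or to the drug that followed. The section on medical record review mentions extraction of TPT-related adverse events, but as an example and without saying who decides relatedness or how. No stated step produces the classification that the table uses.

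**3. Adverse-event monitoring for 3HP**

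- The text on the participant timeline gives patients on 3HP or on TB treatment extra visits that include adverse-event monitoring.
- In Table 1, the TPT rows have adherence monitoring at week 6 and month 3 and no adverse-event row.
- The one adverse-event row in Table 1 has marks at weeks 2, 4 and 8 and months 3, 4, 5 and 6. It sits beside TB-treatment adherence, under a heading for anti-TB therapy.

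Either that heading is meant to include 3HP, which its rows do not suggest, or the table omits what the text promises.

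**The case against.** The strongest reply is that serious events are not ignored. The DMC list includes "6) number and type of serious AEs (SAE" with no TPT restriction, and tables by arm go to its closed sessions. All-cause death is in the primary endpoint and is also a secondary outcome by arm. The safety sentence covers missed prevalent TB and acquired drug-resistant TB as well. Table layouts may sit in the full protocol or an analysis plan. All of this is right, and it rules out saying that no by-arm comparison of all serious events exists or that safety is assessed on TPT harms alone. It does not alter what the article states for the final analysis. That sentence names its categories, and closed DMC tables are not the trial's reported result.

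The 3.7-to-1 ratio is not a bias either. Giving more TPT is what the CRP strategy is meant to do, and more TPT-related events would be a true consequence of it. The weakness is that the count stands without a total beside it.

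A reader might infer three further things, and the documents support none of them:

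- *That the blinded principal investigator is a poor judge of causality.* Blinding to arm protects the attribution. What needs correcting is the object of the judgement.
- *That adverse-event monitoring covers TB treatment and not 3HP.* The participant timeline states that 3HP patients have such visits, and study staff extract interval history at follow-up. The table and text disagree, but monitoring is not absent.
- *That the control arm will suffer more harm from TB treatment.* Study referral for treatment needs a positive urine LAM or Xpert Ultra result, the hypothesis is similar detection of prevalent TB in both arms, and numbers treated are reported by arm. Such harm is possible in either arm. An excess in the control arm is not established.

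**Conclusion.** The point holds as a modest, inexpensive improvement. In the stated analysis, the only adverse events tabulated by arm are those judged TPT-related and serious. About 473 against 129 expected 3HP starters are exposed to that count, and no total or TB-treatment count accompanies it. The classification that it needs is not produced by the causality rule as written. The text and Table 1 must be reconciled on 3HP monitoring.

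The starter numbers rest on the article's planning proportions. The event numbers rest on an assumed risk of 0.5% to 5% per starter, equal in both arms, and only illustrate scale. A reader might go further and call the safety comparison unreliable. The documents do not support that, given the DMC tables, the mortality comparisons and the blinded assessment.

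**What to change.** 1. **Statistical methods.** Tabulate all serious adverse events by arm over all randomized participants, regardless of attribution. Keep the TPT-related count, and add sub-rows for events during TPT and during TB treatment, each also per person treated. The all-randomized row is the comparison protected by randomization. The per-person-treated rows are descriptive, because the two screens select different people for treatment.
2. **Oversight and monitoring.** Replace attribution to the study intervention with two separate judgements, one for relatedness to TPT drugs and one for relatedness to TB-treatment drugs. Keep the assessor blinded to arm.
3. **Participant timeline and Table 1.** Reconcile the two on adverse-event monitoring for 3HP. No monitoring schedule is proposed here.

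The cost is a change of wording in two sections, a second attribution field on the adverse-event form, a correction to Table 1, slightly more data entry and a longer safety table. Serious events are already compiled for the DMC, so little new data collection is needed.
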